### Efficacy evaluation

#### Objectives

The intervention was designed to reduce victimization and perpetration of physical, sexual, and psychological violence in dating (primary outcomes) and to boost the quality of the romantic relationship as well as conflict management skills and help seeking (secondary outcomes).

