#### Recruitment

Several strategies will be used to advertise SOS Dating and recruiting participants: (a) posting on the social networks of social movements related to fighting violence against women, LGBT rights, and youth engagement; (b) advertising on e-mail lists of research associations and research groups interested in related topics; (c) informing the Federal District Ministry of Education, which is connected to public schools frequented by the target audience; and (d) communicating it to student health and guidance services of Brazilian public universities.

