##### Baseline

The included participants will next respond to the baseline evaluation, which will assess attachment style; conflict resolution skills; victimization and perpetration of psychological, physical, and/or sexual violence in their partners; and relationship quality.

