#### Follow-up

At three months after the end of the intervention, the experimental and control group participants will again respond to measurements of conflict resolution skills, victimization and perpetration of violence, and relationship quality. Additionally, they will also fill out the Seeking Help Questionnaire. This instrument, developed by the authors, is composed of three closed questions that inquire whether the respondents sought any sort of help to deal with their affective relationship since they first entered the research website, whom they asked for help, and what the perceived efficacy of the help received was.

Additionally, the Dating SOS participants will be asked to evaluate the impact of the intervention by responding to the Dating SOS Impact Questionnaire, composed of one closed question (How would you evaluate the effects of Dating SOS in your life?) with a multiple choice answer (e.g.: It helped me to end the violent relationship) and three open questions (If Dating SOS made no difference in your life, what do you attribute this to?; If Dating SOS had some effect in your life, what do you attribute this to?; Comment freely about what you thought of Dating SOS).

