### Statistical analysis

Descriptive statistics will be used to describe the characteristics of the participants in the baseline and usability data. The principal analyses will consist of intra- and intergroup comparisons between the baseline and the three-month follow-up on the outcomes of victimization and perpetration of physical, psychological, and sexual violence; quality of the romantic relationship; and conflict management skills. Multivariate analysis of covariance will be used to examine the efficacy of the intervention on these outcomes. The attachment style and the relationship’s violence status will be used as covariates. In addition to this, intergroup comparisons will be conducted using the *t*-test on the three-month follow-up outcome of seeking help. Moderation analysis will be employed to evaluate the differential effects of the intervention based on gender, age, and sexual orientation. A significance level of 0.05 will be adopted.

Omitted or incomplete data will be handled via multiple imputation using the Missing Value Analysis procedure of SPSS Statistics. Intention-to-treat analyses will be carried out, and all randomized participants will be posteriorly included regardless of having completed the intervention or not. The effects of Dating SOS will be estimated utilizing Cohen’s d (where values around 0.2 = small effect size; around 0.5 = medium effect size; and around 0.8 = large effect size).

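### Help seeking is the only stated outcome with no baseline measurement, which costs precision and weakens the handling of the planned 50% dropout

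*Protocol article*

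**What the plan says.** The Objectives under Efficacy evaluation list three secondary outcomes: relationship quality, conflict management skills and help seeking. The Baseline section describes an assessment "which will assess attachment style; conflict resolution skills; victimization and perpetration of psychological, physical, and/or sexual violence in their partners; and relationship quality". Help seeking is not in that list, nor in the sociodemographic survey under Eligibility evaluation.

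The Follow-up section has both arms repeat the conflict, violence and relationship-quality measures, and then adds a new instrument: "Additionally, they will also fill out the Seeking Help Questionnaire". Its first question is whether respondents "sought any sort of help to deal with their affective relationship since they first entered the research website". The others ask who was approached and how useful the help was.

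Statistical analysis treats this outcome separately. Violence, relationship quality and conflict management go into a multivariate analysis of covariance, with attachment style and violence status as covariates. Help seeking gets a between-group t-test "on the three-month follow-up outcome of seeking help". Missing data are to be multiply imputed and the analysis is by intention to treat. The sample-size section allows for 50% dropout.

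One of the four Recruitment channels is "communicating it to student health and guidance services of Brazilian public universities".

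**The concern.** Some participants will probably have had help with their relationship before they entered, or still be receiving it. One recruitment channel runs through services that provide guidance, although the article gives no share. Someone who goes on seeing the same counsellor, or confiding in the same friend, can reasonably answer yes at follow-up in either arm. Nothing in the schedule separates that person from one who sought help for the first time.

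Three things are at stake:

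- **Precision.** Prior behaviour is usually informative about later behaviour, and the comparison cannot use it.
- **Chance imbalance.** A difference between arms in prior help cannot be seen or adjusted for.
- **Missing data.** Randomisation does not protect a comparison of those who stay. If half the sample is lost, imputation can correct only for what was recorded before dropout, and help use at entry was not recorded.

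**Working it through.** **The plan's own figure.** The article gives 610 per arm, based on violence prevalence and not on help seeking. Assuming 50% versus 40%, one-sided 5% and 80% power (neither control rate nor sidedness is stated):

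n = [1.645 × sqrt(2 × 0.45 × 0.55) + 0.842 × sqrt(0.25 + 0.24)]² / 0.10² = 305, and 305 / 0.5 = 610.

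Other assumed inputs also come close. Only the dropout matters here: 610 × 0.5 = 305 completers per arm.

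**Does the missing baseline bias the randomised comparison?** This was simulated with 8,000 trials per setting and deliberately unfavourable assumptions. Everyone in help at entry answers yes at follow-up. Of the others, 20% answer yes in the control arm and 20% (no effect) or 30% (effect) in the intervention arm.

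- No effect, with 0%, 10%, 30% or 50% in help at entry: mean arm difference below 0.1 point in absolute value, rejection rate 4.7% to 5.8%.
- A 10-point effect among the others: expected difference (1 − share in help) × 10, that is 10, 9, 7 and 5 points, and the simulated means agree. These are the true average effects over all participants.
- Power for that effect:

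| In help at entry | 610 per arm | 305 per arm |
|---|---|---|
| 0% | 98% | 82% |
| 10% | 92% | 67% |
| 30% | 69% | 40% |
| 50% | 44% | 26% |

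So there is no bias and no inflation of type I error, but a smaller contrast and less power. The losses are upper limits, because not everyone with earlier help would answer yes to an item about help sought since entry.

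**What would adjustment gain?** Assumed: first question scored yes/no, 20% yes overall, 305 completers per arm, two-sided 5%, 80% power, and correlation r between baseline and follow-up answers.

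- SE = sqrt(2 × 0.2 × 0.8 / 305) = 0.0324
- Detectable difference = 2.80 × 0.0324 = 0.091, or 9.1 points
- With adjustment, multiply by sqrt(1 − r²): r = 0.3 gives 8.7 points (variance down 9%), r = 0.6 gives 7.3 points (variance down 36%)

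**Chance imbalance.** With an assumed 30% in help at entry, the standard error of the arm difference in that share is sqrt(2 × 0.3 × 0.7 / 610) = 2.6 points, or 3.7 points at 305 per arm.

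**Dropout.** An illustration with assumed inputs and no true effect: 30% are in help at entry; 80% of them and 20% of the others answer yes. Control retention is 50% for all. Intervention retention is 65% for those in help and 43.6% for the others: 0.3 × 0.65 + 0.7 × 0.436 = 0.50 overall.

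- Control completers: 0.3 × 0.8 + 0.7 × 0.2 = 38.0% yes
- Intervention completers: share in help = 0.195 / 0.500 = 0.390; 0.390 × 0.8 + 0.610 × 0.2 = 43.4% yes
- Spurious difference: 5.4 points

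With help at entry recorded, imputing within arm and help status restores 38% in both arms and a difference of zero. Without it, imputation corrects only as far as the other baseline variables stand in for prior help. These inputs imply r = (0.3 × 0.7 × 0.6) / sqrt(0.21 × 0.2356) = 0.57, near the top of the assumed range, so the illustration is not a forecast.

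**The case against.** A reader might infer that, without a baseline, help already under way cannot be separated from help the intervention prompted, so that the effect on this outcome is not identifiable. The documents do not support that. Both arms are randomised evenly after baseline and answer the same question, so the control arm supplies the background level. The item asks about help sought since website entry, which excludes help sought only before. No planned analysis lacks its input: baseline-to-follow-up comparisons are specified for the other outcomes only. This objection stands at arm level. It does not help to identify the individual who carries earlier help forward.

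The recruitment argument should also not be pressed. Health and guidance services are one channel of four, and the article speaks of informing them, not of enrolling their clients. The Background reports that adolescent victims rarely seek help. The share in help at entry may be small.

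It can further be said that adjustment gains only 0.4 points at r = 0.3, that it does not undo the dilution (which is a matter of follow-up wording), and that imputation predictors are usually chosen in the analysis plan. The first two are correct. The third does not answer the point, because an analysis plan cannot select a variable that was never collected.

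Finally, an article may omit detail. Here, though, the Follow-up section contrasts repeated measures with an added one, and the item's reference window begins at entry, so this questionnaire as described cannot be a baseline measure.

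**Conclusion.** The point holds as one of precision and missing-data handling for a secondary outcome. Help seeking is the only stated outcome without a baseline value, and its comparison is unadjusted. The randomised comparison in the full sample is unbiased, and the type I error stays near 5%.

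Under the stated assumptions, a baseline item would lower the detectable difference from about 9.1 points to between 8.7 and 7.3. The 20% rate and the correlations are not in the documents. The power losses from continuing help are worst-case and should not be quoted as expected values.

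The stronger reason to act is the planned 50% dropout. The completers' comparison is exposed to retention that differs by arm and prior help, and the imputation lacks a likely strong predictor. How much that matters depends on retention patterns the article cannot give. The primary violence outcomes are not affected.

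**What to change.** - **Baseline.** Add one or two closed items in both arms, before randomisation: whether help with the relationship was sought in the past three months, and whether any is ongoing.
- **Follow-up.** Word the item so that help newly sought since entry is recorded apart from continuing help. This addresses the dilution, which covariate adjustment does not.
- **Analysis.** Replace the unadjusted t-test for this outcome with a comparison that has the baseline answer as covariate. Include that answer in the imputation for this outcome and in the comparison of completers with dropouts.

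Baseline already precedes randomisation, so the design and sample size do not change. The cost is a few seconds per participant and a small chance that the question itself prompts help seeking, equally in both arms. Asking about prior help retrospectively at follow-up is a poor substitute, because the answers would come after exposure and only from those retained.

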### Usability evaluation

With the aim of evaluating the attractiveness of each session and identifying aspects for possible improvement, a usability evaluation will be done at the conclusion of each session of the intervention.

A questionnaire with both open and closed questions, which evaluate the satisfaction of the user with the guidance received and interaction with the tool will be used. Six closed questions investigate satisfaction with the theme of the session, questions, guidance, navigation, quantity of information, and errors. Three open questions examine satisfaction with the layout, guidance content, and suggestions for improvement. Finally, the user is asked which aspect of the Dating SOS was most attractive and which was the least attractive.

### Statistical analysis

Descriptive statistics will be used to describe the characteristics of the participants in the baseline and usability data. The principal analyses will consist of intra- and intergroup comparisons between the baseline and the three-month follow-up on the outcomes of victimization and perpetration of physical, psychological, and sexual violence; quality of the romantic relationship; and conflict management skills. Multivariate analysis of covariance will be used to examine the efficacy of the intervention on these outcomes. The attachment style and the relationship’s violence status will be used as covariates. In addition to this, intergroup comparisons will be conducted using the *t*-test on the three-month follow-up outcome of seeking help. Moderation analysis will be employed to evaluate the differential effects of the intervention based on gender, age, and sexual orientation. A significance level of 0.05 will be adopted.

Omitted or incomplete data will be handled via multiple imputation using the Missing Value Analysis procedure of SPSS Statistics. Intention-to-treat analyses will be carried out, and all randomized participants will be posteriorly included regardless of having completed the intervention or not. The effects of Dating SOS will be estimated utilizing Cohen’s d (where values around 0.2 = small effect size; around 0.5 = medium effect size; and around 0.8 = large effect size).

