#### Calculation of the sample size

The calculation of the sample size for this study uses a conservative procedure to identify a 10% reduction in dating violence prevalence on the intervention group compared to the control group. Adopting a significance level of 5%, a testing power of 80%, and a 50% dropout rate over the course of the study, it was calculated that each condition should have 610 individuals.

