#### Participants and design

An experimental design with a pre-test evaluation and three-month follow-up will be used. Youths between 15 and 29 years of age and their current partners will be invited to participate. A sample of 1220 youths, which will be randomly and evenly divided between the experimental and control groups, is expected. Participants younger than 15 and older than 29 or not currently in a dating relationship will be excluded from the intervention.

The intervention group will receive the SOS Dating intervention, while the control group will receive general information about dating violence, life skills, and sexual and reproductive rights, based on the book “Telling a night out from a trap: a Guide for the Empowerment of Teens in Intimate Relationships” (Diferenciando Baladas de Ciladas: um Guia para o Empoderamento de Adolescentes em Relacionamentos Íntimos) [48], available at http://www.geppsvida.com.br/publicacoes/cartilhas-e-guias/.

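### The efficacy test as described pools the primary violence outcomes with secondary ones, so it can be significant with no effect on violence, and no stated analysis compares the prevalence on which the trial was sized

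*Protocol article*

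**What the plan says.** Three sections of the protocol article bear on this point.

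- **Efficacy evaluation, Objectives.** "The intervention was designed to reduce victimization and perpetration of physical, sexual, and psychological violence in dating (primary outcomes". The same sentence makes relationship quality, conflict management skills and help seeking secondary.
- **Calculation of the sample size.** The calculation "uses a conservative procedure to identify a 10% reduction in dating violence prevalence on the intervention group compared to the control group". Its other inputs are given as "Adopting a significance level of 5%, a testing power of 80%, and a 50% dropout rate over the course of the study", and the result is that "it was calculated that each condition should have 610 individuals". The control prevalence, the sidedness of the test, and whether the 10% is absolute or relative are not stated.
- **Statistical analysis.** The principal analyses cover the violence outcomes, relationship quality and conflict management skills in one list. Then: "Multivariate analysis of covariance will be used to examine the efficacy of the intervention on these outcomes". Attachment style and the relationship's violence status are covariates. Help seeking is tested separately by t-test. "A significance level of 0.05 will be adopted". Effects are expressed as Cohen's d.

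The section on victimization and perpetration describes CADRI items scored on a four-point frequency scale over the whole current relationship. It gives no cut-off that would define a prevalent case.

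**The concern.** The distinction between primary and secondary outcomes made under Objectives does not carry through to the efficacy test. The null hypothesis of a joint MANCOVA is that the intervention affects none of the listed outcomes. Rejecting it shows that something differs between arms, but not that violence does, nor in which direction.

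This could easily arise here. Sessions 2 and 3 work directly on day-to-day relationship quality and conflict handling, so a modest shift on those scales alone is realistic. During pre-testing, professionals also saw a risk of side-effects for users whose relationships were already violent, so the direction of any violence effect matters. The Discussion links wider use in public policy to positive evidence of efficacy. What counts as positive should therefore depend on violence.

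Separately, the sample size rests on a difference between two proportions, while the stated analysis compares mean scores. The hypothesis that the trial was sized for has no matching test.

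**Working it through.** **1. The plan's own figure.** For two proportions with pooled variance under the null,

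n = [z(α)·√(2p̄(1−p̄)) + z(β)·√(p1(1−p1)+p2(1−p2))]² / (p1−p2)².

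With p1 = 0.50, p2 = 0.40, one-sided 5% and 80% power, n = 304.99, rounded to 305. Dividing by (1 − 0.5) for dropout gives 610, the stated figure. The prevalences and the one-sided test are assumptions. Other combinations come close: 0.80 vs 0.70, two-sided with continuity correction, gives 313 and then 626. So 610 is consistent with a comparison of proportions, and the 305 evaluable per arm used below follows from 610 × 0.5.

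**2. Joint test with no effect on violence.** Assume 11 dependent variables: 6 violence (3 types × 2 directions), 2 relationship quality factors and 3 conflict strategies. The subscale counts come from the instrument descriptions; that subscales are entered is an assumption. For two arms of n each, the test is an F test with p = 11 and 2n − 2 − 2 − p + 1 = 596 degrees of freedom (2 for the arms, 2 for covariates). Its noncentrality is

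λ = (n/2)·[Σd² − r(Σd)²/(1+(p−1)r)]/(1−r),

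where r is a common correlation. Put d = 0 on all six violence outcomes and on conflict skills, and d = 0.2 on the two quality factors, so that Σd² = 0.08 and (Σd)² = 0.16.

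- r = 0: λ = 152.5 × 0.08 = 12.2, rejection 62%.
- r = 0.3: λ = 152.5 × 0.0971 = 14.8, rejection 73%.
- r = 0.5: λ = 152.5 × (0.08 − 0.5×0.16/6)/0.5 = 152.5 × 0.1333 = 20.3, rejection 88%.

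With 0.2 SD on all five secondary scales, rejection is 96% to 99%. At 610 per arm the two-factor case gives 94% to 99.8%. The plan itself calls a d of 0.2 small.

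**3. Sensitivity to the count of 11.** If quality and conflict skills each enter as one score (p = 8) and only quality shifts by 0.2 SD, then λ = 152.5 × 0.04 = 6.1 at r = 0 and 152.5 × (0.04 − 0.5×0.04/4.5)/0.5 = 10.8 at r = 0.5. Rejection is 36% and 62%: lower, but still far above 5%.

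**4. Power for an effect on one violence outcome.** A d of 0.227 gives power 0.80 for a single outcome at 305 per arm. With 11 outcomes the power is 0.40 at r = 0 and 0.71 at r = 0.5. With 6 it is 0.52 and 0.79. The loss depends on correlation and can nearly vanish.

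**5. Cost of splitting alpha.** Two-sided power for proportions at 305 evaluable per arm, at 0.05 and at Holm's first step (0.025):

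| Assumed prevalences | 0.05 | 0.025 |
|---|---|---|
| 0.50 vs 0.40 | 0.70 | 0.60 |
| 0.80 vs 0.70 | 0.82 | 0.73 |

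**The case against.** The strongest reply is that the text names a method, not a number of models or a decision rule. One MANCOVA per domain would fit the same words and would remove the mixing problem. Intergroup comparisons and Cohen's d could be reported per outcome and with sign, which would make a null or harmful violence result visible. This stands in part. A single joint test is the plain reading, since the sentence refers back to the whole list, but it is not explicit. Even with separate models, no stated rule makes the efficacy conclusion depend on violence, and the mismatch with prevalence remains.

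It can also be said that analysing frequency scores usually loses less information than a dichotomy, so the mismatch need not be harmful. That is fair, but the stated power then refers to a test that is not planned.

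Three stronger readings are tempting and are not supported:

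- **Dilution as the main fault.** A reader might infer that the joint test halves power for violence. The 0.40 requires uncorrelated outcomes and an effect on only one of them. CADRI asks one respondent about one relationship, so zero correlation is implausible.
- **Family-wise error of about 26%.** That is 1 − 0.95^6, for six independent univariate tests. The article does not say that efficacy will be read from univariate tests, and follow-up testing may be set out in a document not shown.
- **A wrong sample size.** The 610 can be reproduced, and the unstated inputs do not allow it to be called an error.

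The 305 is a complete-case figure. The plan imputes missing data and analyses all randomized participants, so the effective number may be larger, which raises the rejection rates in step 2.

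**Conclusion.** The concern holds in this form: the efficacy test, on its plain reading, joins primary and secondary outcomes at one 0.05 level, and no analysis of the sized quantity is stated. A significant result would not establish an effect on violence. With no violence effect and a small shift in the two quality factors, the chance of rejection is 62% to 88% at 305 per arm. This assumes 11 dependent variables, equal correlations from 0 to 0.5 and d = 0.2. The exact figure moves with these assumptions; the conclusion does not. Confidence is high on the conflict between the three sections and lower on whether one model is intended, which the authors can settle in a sentence.

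**What to change.** 1. State a primary efficacy test on violence alone, covering victimization and perpetration, adjusted for the baseline violence scores already collected. Control the error rate across the two directions, for example with Holm, and report signed effects with intervals.
2. Move relationship quality and conflict skills to a separate secondary model whose result does not enter the efficacy claim.
3. Reconcile the sample size section with that test, in one of two ways. Either compare prevalence between arms, define a case, and have the follow-up CADRI refer to the period since baseline; or keep the score analysis and restate the sample size justification for it. A yes/no outcome on the present wording would not work: someone already exposed and still with the same partner cannot, if answering consistently, become a non-case.

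**Cost.** Items 1 and 2 change analysis wording and need no new data. The prevalence option changes the recall period of one follow-up instrument. The score option needs a new calculation. Splitting alpha lowers power for each test by the amounts in step 5, so the stated 80% should be restated and, depending on the assumed prevalence, the sample size revisited. The change should be made before outcome data are examined by arm.

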#### Step 6: Intervention pre-testing

Next, the intervention’s pre-testing was performed. Three pre-testing sessions were held, the first with three young people potential users, the second with three professionals working at centers for victims of domestic violence, and the third with twenty university students. The main findings of pre-testing were related to the format and content:
The young people potential users thought the messages were too long and that SOS Dating’s interface was not clear;The professionals noted a risk for side-effects in the guidance regarding the bidirectional violence and conflict management for participants whose relationships were already violent.All participants reported perceiving the intervention as relevant.Responding to these findings, an extensive review was performed of the intervention’s visual aspects and content.A new visual identity, aiming for greater interface elements clarity, was proposed and content readability was improved.The messages were shortened to reduce the cognitive demand on the participants;Tailoring adjustments were made in conflict management and actions plans regarding the status of violence in the relationship, with the purpose of preventing iatrogenic effects and boosting participant identification with the intervention.

After these adjustments, new wave of pre-testing was done with two potential users and two experts in domestic violence, which approved the aforementioned changes.

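### The efficacy model names no outcome's own baseline score as a covariate, which costs precision, and within-arm change is listed among the principal analyses

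*Protocol article*

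**What the plan says.** All references are to the protocol article.

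- **Model and covariates.** The Statistical analysis section names a multivariate analysis of covariance for efficacy. Attachment style and the relationship's "violence status will be used as covariates". No other covariate is listed.
- **Principal analyses.** The same section states: "The principal analyses will consist of intra- and intergroup comparisons between the baseline and the three-month follow-up". The outcomes listed there are violence (victimization and perpetration), relationship quality and conflict management.
- **What is measured, and when.** The Baseline section says: "The included participants will next respond to the baseline evaluation". That evaluation covers attachment, conflict resolution, violence and relationship quality. The Randomization section places allocation after it. The Follow-up section repeats the violence, relationship-quality and conflict measures at three months. Help seeking is asked only at follow-up.
- **Violence status.** The Intervention section gives three degrees (none, episodes, regular) and adds direction where violence is present. How this is coded as a covariate is not stated.
- **Moderators.** Gender, age and sexual orientation.
- **Sample size.** The target is to "identify a 10% reduction in dating violence prevalence on the intervention group compared to the control group", with "a 50% dropout rate over the course of the study", giving 610 per arm.

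**The concern.** In a randomised trial the baseline value of an outcome is usually its best single predictor at follow-up. Here those values are in hand before allocation, but the named covariates leave them out. Relationship quality and conflict skills are represented only indirectly, through attachment and violence status. Violence is represented by a coarse category derived from its own scale. With half the sample expected to be lost, unused precision matters.

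The second issue is the place given to within-arm comparisons. A pre-post change in one arm mixes any effect with time trends, regression to the mean and selective dropout. Calling it a principal analysis leaves room for reading significance in one arm but not the other as evidence of efficacy.

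**Working it through.** **1. The plan's own figure.** The inputs are "Adopting a significance level of 5%, a testing power of 80%, and a 50% dropout rate over the course of the study". The control rate and sidedness are not given. Assuming 50% against 40%, one-sided 5% and pooled variance:

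n = [1.645·√(2·0.45·0.55) + 0.842·√(0.25 + 0.24)]² / 0.10² ≈ 305 per arm, and 305/(1 − 0.5) = 610.

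This matches exactly. The two-sided version gives 388, inflated to 776. The target rests on a comparison of two proportions, so the choice of covariates does not alter it. I take 610 × 0.5 = 305 completers per arm below.

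**2. Follow-up scores as the dependent variables.** Let r be the correlation between baseline and follow-up. The documents do not give it, so I assume a range. In units of the unadjusted variance, adjustment for the outcome's own baseline leaves 1 − r². The variance of an analysis with no covariates, relative to that, is 1/(1 − r²).

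**3. Change scores, or group by time.** The variance is 2(1 − r). Relative to own-baseline adjustment this is 2(1 − r)/(1 − r²) = 2/(1 + r).

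| r | Follow-up score, 1/(1 − r²) | Change score, 2/(1 + r) |
|---|---|---|
| 0.3 | 1.10 | 1.54 |
| 0.5 | 1.33 | 1.33 |
| 0.7 | 1.96 | 1.18 |

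**4. Allowing for the covariates already named.** Both columns assume no other adjustment, so they are upper limits wherever attachment and violence status explain part of the baseline score. As an illustration, assume that they explain 30% of it and act only through it.

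- Follow-up scores at r = 0.6: the planned model leaves 1 − 0.30·0.36 = 0.892, and own-baseline adjustment leaves 0.64. The saving is 1 − 0.64/0.892, about 28%, against 36% with no covariates.
- Change scores at r = 0.6: the ratio is 1 + 0.70·(1 − 0.6)/(1 + 0.6) = 1.175, against 2/1.6 = 1.25.

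**5. Violence outcomes as follow-up scores.** Take status as a three-level cut of the same baseline score. This is the case most favourable to the plan. Under a normal model such a cut keeps a share q of about 0.75 to 0.80 of the baseline information. The ratio (1 − q·r²)/(1 − r²) is 1.02 at r = 0.3, 1.07-1.08 at 0.5 and 1.19-1.24 at 0.7.

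**6. Detectable difference.** With 305 per arm, two-sided 5% and 80% power, the unadjusted figure is (1.960 + 0.842)·√(2/305) = 0.227 SD. Multiplying by √(1 − r²) gives 0.216 at r = 0.3, 0.196 at 0.5 and 0.162 at 0.7. The plan itself labels values around 0.2 a small effect.

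**7. Within-arm tests.** Assume no treatment effect and the same drift of 0.10 SD in both arms. The standard error of the mean change is √(2(1 − r)/305): 0.057 at r = 0.5 and 0.044 at r = 0.7. The intervention arm alone then shows a significant change with probability 0.42 and 0.62 respectively. Significant in the intervention arm but not in control has probability 0.416 × 0.584 = 0.24 and 0.616 × 0.384 = 0.24. With no drift it is 0.047. With larger drift it falls again, because both arms become significant (0.06 at 0.20 SD and r = 0.5).

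The violence scale adds a difficulty: it counts events in the current relationship. Within one continuing relationship a true cumulative count cannot fall, so pre-post change is hard to interpret.

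**The case against.** The strongest reply is that the article leaves the form of the dependent variables open. Since the comparisons run from baseline to three months, baseline may well enter as a time factor, so a reader who infers that baseline is ignored goes beyond the text. That stands. However, a time factor yields a change comparison, which is not the same as covariate adjustment and is still less precise (step 3).

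It is also fair that the full 1 − r² saving cannot be claimed. The article's own theory section ties attachment to relationship quality and conflict resolution, so part of the gain is already taken (step 4). For violence, the primary outcome, the loss at moderate r is small when follow-up scores are analysed. Status also includes direction, so three levels may understate what it carries.

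A reader might infer that the plan intends to claim efficacy from within-arm change. It does not say so: efficacy is assigned to the multivariate model, and the within-arm listing is a risk of misreading.

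A reader might also infer that the plan hides a known harm, because pre-test professionals noted "a risk for side-effects in the guidance regarding the bidirectional violence and conflict management for participants whose relationships were already violent" and violence status is not a moderator. The same section reports that the tailoring was then changed to prevent such effects, and that a further round including two domestic-violence experts approved the changes. Gender, age and sexual orientation are legitimate moderators, and nothing in the documents requires replacing them.

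**Conclusion.** The point holds as a matter of precision and labelling. The planned model is less precise than one that adjusts each outcome for its own baseline, under either reading of the dependent variables. The variance ratio is at most 1.10 to 1.96 for follow-up scores and 1.54 to 1.18 for change scores as r runs from 0.3 to 0.7, and is smaller where the named covariates already explain part of baseline. For violence as follow-up scores it is about 1.02 to 1.08 at r of 0.3 to 0.5.

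These figures rest on assumed r, a normal model for the coarse category, and completers as the measure of information. Randomisation keeps the between-arm contrast unbiased, so the documents do not support calling the efficacy analysis invalid. The 610 per arm stands apart from this issue. Help seeking has no baseline measure and is not affected. Within-arm comparisons carry no randomised evidence and should not rank as principal.

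**What to change.** Keep the planned multivariate model, with three-month scores as the dependent variables, and add each outcome's own baseline score to attachment style and violence status. In a standard multivariate model every covariate enters for every outcome. If the scales are scored by type or factor, this is about 6 + 2 + 3 = 11 extra terms (violence, relationship quality, conflict resolution), which is small against about 610 completers. Overlap between violence status and the violence scores does not harm the arm contrast.

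State that efficacy is judged only on the between-arm contrast at three months, and that within-arm change is descriptive.

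Optionally, add an exploratory arm-by-baseline-violence-status estimate with confidence intervals beside the planned moderators, because the content is tailored on that variable.

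The cost is analysis wording only. All variables are already collected before randomisation, and the sample size does not change.
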